## Abstract

**Introduction:**

The majority of preventable deaths in healthcare are due to errors on general wards. Staff perceptions of safety correlate with patient survival, but effectively translating ward teams’ concerns into tangibly improved care remains problematic. The Hospital Event Analysis Describing Significant Unanticipated Problems (HEADS-UP) trial evaluates a structured, multidisciplinary team briefing, capturing safety threats and adverse events, with rapid feedback to clinicians and service managers. This is the first study to rigorously assess a simpler intervention for general medical units, alongside an implementation model applicable to routine clinical practice.

**Methods/analysis:**

7 wards from 2 hospitals will progressively incorporate the intervention into daily practice over 14 months. Wards will adopt HEADS-UP in a pragmatic sequence, guided by local clinical enthusiasm. Initial implementation will be facilitated by a research lead, but rapidly delegated to clinical teams. The primary outcome is excess length of stay (a surplus stay of 24 h or more, compared to peer institutions’ Healthcare Resource Groups-predicted length of stay). Secondary outcomes are 30-day readmission or excess length of stay; in-hospital death or death/readmission within 30 days; healthcare-acquired infections; processes of escalation of care; use of traditional incident-reporting systems; and patient safety and teamwork climates. HEADS-UP will be analysed as a stepped wedge cluster controlled trial. With 7840 patients, using best and worst case predictions, the study would achieve between 75% and 100% power to detect a 2–14% absolute risk reduction in excess length of stay (two-sided p<0.05). Regression analysis will use generalised linear mixed models or generalised estimating equations, and a time-to-event regression model. A qualitative analysis will evaluate facilitators and barriers to HEADS-UP implementation and impact.

**Ethics and dissemination:**

Participating institutions’ Research and Governance departments approved the study. Results will be published in peer-reviewed journals and at conference presentations.

**Trial registration number:**

ISRCTN34806867.

Strengths and limitations of this studyGeneral wards typically generate the errors that lead to preventable deaths, but we know relatively little about how to improve the safety of care in this specific setting.This study will evaluate a new strategy to incorporate proactive team risk surveillance into routine care on general medical wards, with a facilitated organisational response: Hospital Event Analysis Describing Significant Unanticipated Problems (HEADS-UP).Mixed methods (quantitative and qualitative) will identify different aspects of the impact of HEADS-UP.With a relatively prolonged data collection period, the study is prey to unanticipated changes affecting participating sites.

## Background

### Patient safety on medical wards

Despite an intense focus on healthcare safety in recent years, medical wards remain potentially perilous. Over 60% of medical wards’ failings reach their patients, and 10% of those failings cause physical injury.^1^ These are not trivial problems: the general ward, more than any other care setting, generates the errors that lead to preventable deaths.^2^ Technical procedural failings are infrequent; more often, teams struggle to reliably monitor, assess and reassess their patients.^2^ Medical teams face increasing workloads,^3^ and concerns about the basic processes of ward care have been well publicised.^4^

Nonetheless, there is a relative paucity of specific literature on how to improve the quality and safety of care on medical wards. The same factors that contribute to serious errors in this setting—heterogeneous patient populations, geographic dispersion of medical teams, and frequent changes in staff, policies and procedures—have hampered the research necessary to address them. As a result, quality and safety interventions for medical patients are largely extrapolated from more structured clinical environments, that is, operating theatres and intensive care units (ICUs). Staff in medical units, however, would rapidly attest to the different challenges they face, compared to their colleagues in these other areas.

A recent review by our group established that interventions to improve medical ward care cluster across five themes:^5^
Improving staffing levels and team composition;Improving communication and collaboration;Standardising care processes;Early recognition and treatment of the deteriorating patient;Improving patient safety climate.

Although the evidence base underpinning them is fragmented, these interventions are likely to have some positive impact on the quality and safety of care. Organisations increasingly adopt multifaceted improvement strategies that incorporate combinations of these five themes.^6^
^7^ These complex strategies are highly specific to their setting, and may be costly to implement.^8^ This limits their wider applicability, and a search for a more universally relevant tool is warranted.

### Frontline ward staff: a knowledgeable, but underused, source of information

Frontline staff are a relatively untapped source of information about their own organisation and the effectiveness of its procedures and processes. It matters, what staff say: their perceptions correlate with patient survival.^9^ Moreover, finding the right tools to elicit staff concerns might facilitate change: organisations that seek out discomfiting insights, consciously listening to their staff, develop more holistic improvement strategies.^10^ Still, there are few descriptions of successful tools that systematically capture staff knowledge to improve clinical processes. Centralised incident reporting systems have major failings,^11^
^12^ and physicians as a professional group do not engage with them.^11^ Improving reporting systems is a laudable goal, but additional methods are required to adequately detect and address problems before they lead to adverse events and patient harm.^13^

Importantly, the problem may lie with the available tools themselves, not their users. Ward staff are willing to disclose concerns about errors and potential errors to their peers,^14^ and incident reporting rates increase when clinicians are given more reporting options and receive feedback.^15^ Interactive schemes, visibly engaging entire teams to identify recurrent problems, may complement more traditional systems relying on individual reports.^16^
^17^ There is increasing interest in novel strategies to take advantage of team knowledge: for medical teams, the ward round may represent a specific opportunity to identify patient safety issues.^18^ Moreover, studies in paediatric centres suggest that patient-relevant process measures improve with a structured team approach to risk monitoring and situational awareness (eg, ‘team huddles’).^19^
^20^ It seems that a collective awareness of safety problems exists; exploiting it may have real benefits, beyond the typical reliance on individual efforts to intercept a catastrophic clinical deterioration, or report it after the event.

In our review,^5^ we identified no reports of simple interventions which (1) specifically targeted adult medical wards; (2) leading to team-wide engagement in a quality and safety initiative; with (3) rigorous assessment of patients’ clinical outcomes. More complex interventions in this field have been tailored to the specific needs of individual clinical trial sites, or require resource-intensive support and mentoring,^21^ which limit their uptake in wider practice. Moreover, there are few reports of community hospitals replicating the experience of academic centres.^22^

The HEADS-UP (Hospital Event Analysis Describing Significant Unanticipated Problems) study that we describe here addresses these limitations with a tool that can be rapidly and easily adopted in any healthcare context. Our intervention aims to identify and mitigate systematic failings through daily whole-team recognition of clinical risks, facilitating improved team situational awareness, allied to a rapid organisational response.

### The HEADS-UP intervention

A prompt-led team briefing (HEADS-UP) was designed to help multidisciplinary medical ward teams discuss clinical and administrative challenges, including adverse events, of the preceding 24 h. The briefing can be led by any member of the team, regardless of seniority or role. HEADS-UP identifies ongoing concerns amenable to immediate intervention, as well as those requiring more detailed assessment and input from other departments. It also prompts team members to share information that they may not volunteer spontaneously.^23^
^24^ Categories of prompts were guided by the published literature on the nature of common unintended events in medical departments^1^ (figure 1), with additional suggestions from ward clinicians regarding frequent or potentially serious lapses in care noticed in their clinical areas. At the request of participating physicians, a checklist-style pro-forma was used to facilitate speed of completion. We adopted a visual format similar to the World Health Organization's surgical safety checklist (figure 2). HEADS-UP summaries are regularly disseminated to participating teams, senior clinicians, managers and executives.

**Figure 1 BMJOPEN2014007510F1:**
[figure not shown]
Categories of unintended events in internal medicine departments impacting negatively on patient care (after Lubberding *et al*^1^).

**Figure 2 BMJOPEN2014007510F2:**
[figure not shown]
The HEADS-UP (Hospital Event Analysis Describing Significant Unanticipated Problems) team briefing tool.

### Study aim and hypotheses

The primary aim of this study is to assess the impact of the HEADS-UP briefing tool on clinically relevant patient outcomes. The secondary aim is to explore how changes in patient outcomes, if any, are mediated by changes in workplace climate and ward processes.

We hypothesised that:
Team use of the HEADS-UP briefing would empower junior clinicians to voice concerns, improving their teams’ situational awareness (an important factor in mitigating risks^19^) and their units’ safety and teamwork climates;This would promote early team recognition of the deteriorating patient, and facilitate the process of escalation of care;Information generated by ward teams would both inform their own practice and prompt downstream service reorganisation;The combination of ward and support service improvement would improve clinical outcomes, with a dose-response relationship (ie, the better the tool is used in practice, the greater the benefit seen);An explicit focus on team-wide recognition of adverse events would improve engagement with existing incident-reporting systems, thus leading to an increase in formally reported incidents within wards implementing HEADS-UP.

## Methods and design

### Study design and setting

HEADS-UP is a prospective stepped wedge, cluster controlled trial, conducted in two hospitals in London, UK. The stepped wedge design involves the sequential introduction of the intervention to each of the clusters (in this case, wards) over time, with clusters progressively moving from the control group to the intervention group (figure 3). The staged implementation facilitated by the stepped wedge design is particularly helpful when simultaneous rollout of an intervention to all clusters is impractical, for example, for logistical or financial reasons. This trial design is used to evaluate interventions whose effects are predicted to be more beneficial than harmful, especially those interventions embedded in daily clinical practice.^25^ Stepped wedge designs are increasingly used in trials of interventions in acute care.^26–29^

**Figure 3 BMJOPEN2014007510F3:**
[figure not shown]
HEADS-UP (Hospital Event Analysis Describing Significant Unanticipated Problems) stepped wedge cluster design.

The order in which clusters receive the intervention will be guided by logistical restrictions, and the de facto recognition of clinicians enthusiastic to introduce HEADS-UP to their wards. Although cluster randomisation (randomising the order in which the clusters receive the intervention) would be preferable, it is important to recognise the impact of willing early adopters who then lead their colleagues in implementing the intervention.^30^ They are likely to participate more extensively and follow through more rigorously and enthusiastically with the intervention than units at later stages of the intervention diffusion.^31^ Sufficient leadership and support from these early adopters will be needed to maximise the use of HEADS-UP in all the desired areas, much as the introduction of surgical checklists, for instance, has historically relied on strong clinical leadership.^32^ HEADS-UP is introduced to new clusters at two-monthly intervals.

The study is conducted at two sites. The first is a university-associated community general hospital. Clusters from this site are generated from the acute admissions and downstream medical (gastroenterology, respiratory and geriatric) wards. Each cluster comprises clinical areas that are physically linked, served by the same medical team, or both. This will help to limit contamination between groups. The second site is an academic hospital, where HEADS-UP will be implemented within the geriatric wards.

### Study population

The study focuses on adult medical patients admitted to study wards between 2013 and 2015. To isolate the effect of the intervention, patient-level exclusion criteria will include:
Time spent on the specified ward comprising less than 50% of the total inpatient stay;Discharge to a new skilled care facility or other hospital (ie, not the patient's address at the time of admission; discharge to a new facility typically incurs substantial delays, outside of the ward team's control);Multiple intrahospital ward transfers. A single transfer from the initial admissions unit to a downstream medical ward is permitted. One further transfer to an escalation area to facilitate discharge (whereby the patient spends less than 24 h in the escalation area immediately prior to their discharge home) is also permitted;Admission to the high-dependency unit, or ICU;Elective admission or direct admission from another hospital;Surgeon-directed care for more than 24 h during the inpatient stay.

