### Outcome measures

*Primary outcome*
Excess length of stay (eLOS)—a surplus stay of 24 h or more, compared to peer institutions’ Healthcare Resource Groups-predicted length of stay.

*Secondary outcomes*
eLOS or 30-day readmission;In-hospital death or death/readmission within 30 days;Complications of care: hospital-acquired infections and pressure ulcers;Processes of escalation of care: use of the ICU outreach service, admissions to the ICU, and cardiac arrest calls;Staff engagement with the traditional web-based reporting system: number, and type (eg, patient falls or communication failures) of formally reported incidents;Patient safety climate: teamwork and safety subsections of the well validated Safety Attitudes Questionnaire (SAQ).^33^

We believed that tangible improvements in clinical outcomes and quality of care would be mediated by changes in ward processes, and ward safety and teamwork climates. Our chosen outcomes allow us to evaluate this hypothesis. The selected measures are similar to those used in other studies evaluating the quality of ward care,^34^ and have been assessed in a UK setting where appropriate.^33^
Table 1 describes specifically how the components of these outcomes correspond to the study hypotheses outlined earlier.

**Table 1 BMJOPEN2014007510TB1:** Study outcomes and corresponding hypotheses evaluated within the HEADS-UP trial

	Outcome component	Relevant hypothesis	Rationale for outcome selection
Primary outcome	Excess length of stay	Improved clinical outcomes through ward and support service improvements	Length of stay reflects efficient resource use, and possibly quality of care.^35^ Length of stay varies substantially within institutions, with wide differences between the acute admissions unit and downstream wards. Using excess length of stay as an outcome increases study power, facilitating statistical detection of a meaningful change in outcome without requiring an excessive number of wards or data collection period.

Secondary outcomes: clinical outcomes	Mortality	Improved clinical outcomes through ward and support service improvements	Correlates with quality of care^36^ and may relate to performance in non-technical skill domains.^37^

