	Readmission	Improved clinical outcomes through ward and support service improvements	Need to confirm that improvements in hospital efficiency do not come at the expense of increased readmissions. 37% of medical readmissions are avoidable,^38^ a proportion that can be reduced with targeted quality improvement initiatives.^39–41^
	Complications of care	Improved situational awareness will mitigate patient risks	Agreement that these outcomes are appropriate patient safety indicators.^42^ Reliable reporting of these outcomes to confirm adherence to stringent centrally mandated targets.^43^ ^44^

Secondary outcomes: processes of care	Escalation of care	Earlier team recognition of the deteriorating patient will facilitate processes underpinning escalation of care	Multidisciplinary interventions, increasing team situational awareness,^45^ may address staff reluctance to appropriately escalate their concerns.^24^ ^46^

Secondary outcomes: staff outcomes	Staff engagement with traditional reporting system	Team-wide recognition of adverse events will improve engagement with existing incident reporting systems	More reports overall, with a lower contribution from reports of slips and falls, are associated with more positive safety culture and risk management ratings.^47^
	Safety and teamwork climate	Empowerment of junior clinicians, with structured communication tool, will improve perceptions of safety and teamwork	Improved safety climate is associated with organisation-wide reduction in adverse events.^48^ SAQ scores previously assessed both in inpatient settings and in the UK.^33^

HEADS-UP, Hospital Event Analysis Describing Significant Unanticipated Problems; SAQ, Safety Attitudes Questionnaire.

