Given the variation in baseline outcomes in our local data set, we then estimated the study's power to detect a 1 standard deviation reduction in eLOS on the wards with the highest and lowest baseline outcome rates. With 7840 patients in the trial (560 patients/month), and two-sided p<0.05, the study would achieve 100% power to detect a 14% absolute risk reduction. At worst, in the ward with the lowest baseline outcome rate, it would achieve 75% power to detect a 2.3% absolute risk reduction. We therefore propose that the study's power to detect a 2–14% absolute risk reduction lies between 75% and 100%. With this complex trial design, statistical uncertainty in power calculations is not unusual. The recent protocol of a large stepped wedge cluster randomised trial similarly produced a range within which its power might lie.^29^ Experts also advocate more widespread recognition of the inherent limitations of statistical power thresholds.^59^

The stepped wedge design compares outcomes in each cluster before and after the introduction of the intervention. Overall differences in outcomes between preintervention and postintervention periods will be reported. Primary analysis will be on an intention-to-treat basis, with a separate prespecified per-protocol analysis of those units implementing the intervention with high fidelity. Analyses will use the patient-level data described above, clustered within ‘units’, using random effects to model the correlation between individuals within the same cluster. Generalised linear mixed models, or generalised estimating equations, will form the basis of the analysis.^57^ Results will also be assessed using a time-to-event regression model. Underlying temporal trends (including seasonal trends) will be accounted for. We will evaluate any interaction effect between intervention group and ‘duration of HEADS-UP implementation’ to see if the intervention exerts an incremental effect over time. There will be a prespecified analysis excluding patients coded for palliative care, to further isolate the effect of the intervention. Sensitivity analyses will judge whether primary outcome results remain unchanged when other patient groups (eg, those spending less than 50% of their stay on the specified ward) are included. No interim analyses are planned, nor is a formal health economics analysis.

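### HDU/ICU admission is an exclusion for every outcome although ICU admissions are a secondary outcome: that component is zero as written, and eLOS and mortality are selected on an event the intervention may change

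*Protocol article*

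**What the plan says.** In the protocol article, Study population introduces the exclusions with "To isolate the effect of the intervention, patient-level exclusion criteria will include". One of the listed criteria is "Admission to the high-dependency unit, or ICU". No outcome is exempted from it.

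Outcome measures defines the escalation-of-care secondary outcome as "use of the ICU outreach service, admissions to the ICU, and cardiac arrest calls". Study aim and hypotheses says of the briefing: "This would promote early team recognition of the deteriorating patient, and facilitate the process of escalation of care". Table 1 gives as rationale that interventions of this kind "may address staff reluctance to appropriately escalate their concerns".

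Sample size, power calculation and analysis states "Analyses will use the patient-level data described above". On relaxing the exclusions it says "Sensitivity analyses will judge whether primary outcome results remain unchanged when other patient groups" are added back. The one example given is patients who spent under half their stay on the ward. HDU/ICU patients are not named, and the secondary outcomes are not covered.

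**The concern.** There are two separate problems.

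The first is a contradiction. An event that removes a patient from the analysed population cannot also be counted in that population. The other two escalation components are affected in part: an outreach referral or arrest call that ends in HDU or ICU drops out with the patient, so the escalations that led to transfer are the ones lost.

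The second is selection after exposure. HDU/ICU admission can happen after the patient has come under the ward's care, and escalation is one of the processes HEADS-UP is meant to alter. If the intervention changes who is transferred, the patients left in the control and intervention periods are no longer alike. eLOS and mortality could then differ between periods with no true effect on either, or a true effect could be hidden.

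At stake are one component of a secondary outcome, which cannot be estimated as written, and the reading of any modest difference in eLOS or mortality.

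**Working it through.** **1. The passages side by side**

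| Section | Content | Consequence |
|---|---|---|
| Study population | HDU/ICU admission excludes the patient, for all outcomes | Analysed set has no HDU/ICU patients |
| Outcome measures | ICU admissions are an outcome component | Count in the analysed set is 0 in both periods |
| Outcome measures | Outreach use and arrest calls are also components | Countable, but only in patients not admitted to HDU/ICU |
| Sample size, power calculation and analysis | Analyses use the patient-level data already described | No wider population is given for escalation |
| Study aim and hypotheses; Table 1 | HEADS-UP should ease escalation | Exclusion may depend on the intervention |

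**2. The plan's own power figure**

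This gives a yardstick only; the point does not depend on it. 560 patients/month × 14 months = 7840. I used the Hussey–Hughes stepped-wedge variance with 7 clusters, 7 periods of 160 patients per cluster-period, ICC 0.06 and total variance 0.056 × 0.944 = 0.05286. The standard error is 0.00875. Power for 2.3 points is Φ(0.023/0.00875 − 1.96) = 74.8%, against 75% stated. With 8 periods of 140 it is 74.0%. For 14 points from 51.5% it is 100%, as stated. So 2.3 points is the smallest effect for which the plan states a power.

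**3. Size of the selection effect**

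All rates here are assumed, except that 5.6% is the article's lowest baseline eLOS rate. Let
- p = outcome risk in the control-period analysed set,
- q0, q1 = proportion admitted to HDU/ICU in the control and intervention periods,
- r = outcome risk in the patients whose transfer status changes.

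With no true effect on the outcome, the intervention-period rate is

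[p(1 − q0) − (q1 − q0)r] / (1 − q1),

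so the artefact is

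(q1 − q0)(p − r) / (1 − q1).

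It is zero if q1 = q0. Its sign depends on whether ICU use rises or falls and on whether r exceeds p.

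*Rises in ICU use.* I took q0 from 1% to 4% and q1/q0 from 1.25 to 2. For eLOS the pairings were p = 25% with r = 60% or 80%, and p = 5.6% with r = 60%. For mortality, p = 5% with r = 30% or 40%.

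| Outcome | p | q0 → q1 | r | Calculation | Artefact (points) |
|---|---|---|---|---|---|
| eLOS, smallest | 25% | 1% → 1.25% | 60% | 0.0025 × (−0.35)/0.9875 | −0.09 |
| eLOS, middle | 25% | 2% → 3% | 80% | 0.01 × (−0.55)/0.97 | −0.57 |
| eLOS, largest | 25% | 4% → 8% | 80% | 0.04 × (−0.55)/0.92 | −2.39 |
| eLOS, lowest baseline | 5.6% | 4% → 8% | 60% | 0.04 × (−0.544)/0.92 | −2.37 |
| Mortality, smallest | 5% | 1% → 1.25% | 30% | 0.0025 × (−0.25)/0.9875 | −0.06 |
| Mortality, largest | 5% | 4% → 8% | 40% | 0.04 × (−0.35)/0.92 | −1.52 |

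The upper ends are set by the assumptions. Pairing p = 5.6% with r = 80% at 4% → 8% would give 0.04 × (−0.744)/0.92 = −3.2 points.

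*A fall in ICU use.* With 4% → 2%, eLOS at p = 25% and r = 80% gives (−0.02) × (−0.55)/0.98 = +1.12 points. Mortality at p = 5% and r = 40% gives (−0.02) × (−0.35)/0.98 = +0.71 points. A real benefit would be masked.

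*Similar risks.* At p = 51.5%, r = 50% and 3% → 6%, the artefact is 0.03 × 0.015/0.94 = +0.05 points, practically nil.

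**The case against.** The strongest reply is that the sentence on patient-level data cannot govern every outcome. Incident reports and staff SAQ scores have no patient-level denominator, and Table 1 lists escalation as a process of care, apart from the clinical outcomes. The investigators may have meant ward-level counts, with the detail left to a fuller document. That is plausible. But the article does state a population and an exclusion, exempts nothing, and names as an outcome the event it excludes. Ward-level counting would also leave the selection in eLOS and mortality untouched.

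Second, leaving out stays partly determined outside the ward is a defensible choice for a ward length-of-stay endpoint, and the stated sensitivity analyses are introduced with a non-exhaustive example, so HDU/ICU patients may be among the groups added back. This stands for eLOS. It does not reach mortality or escalation, because those analyses are confined to the primary outcome.

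Third, simply deleting the exclusion would be an incomplete remedy. The multiple-transfer and 50%-stay rules would still remove many of these patients, and the planning rates came from patients who met the current criteria. This stands too, and it is why the primary population need not change.

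A reader might infer three stronger conclusions. None is supported:
- *That the escalation hypothesis cannot be tested at all.* Only the ICU-admission component is empty; the other two are truncated.
- *That the exclusion makes HEADS-UP look better.* The article says escalation should be eased, not that ICU admissions should rise. Earlier recognition could lower them, and the bias would then reverse.
- *That the bias is known to be large against the 2.3-point effect.* That effect was set for the ward with the lowest baseline rate, the largest artefacts need a doubling of ICU use, and the article gives no ICU rate.

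**Conclusion.** The point holds in two parts. By the article's own wording, the ICU-admission component is zero in both periods and cannot show an effect, while outreach use and arrest calls are restricted to patients who stayed out of HDU/ICU. This part needs no assumption beyond reading the three sections together.

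The main eLOS and mortality comparisons also condition on an event that the intervention may change. The resulting bias is conditional and has no known direction. It is zero if HDU/ICU admission is unaffected. Over the assumed rises in ICU use and the pairings shown, it is a spurious reduction of about 0.1 to 2.4 points in eLOS and 0.1 to 1.5 points in mortality; a fall in ICU use reverses the sign. These sizes are illustrations, not estimates for these wards. They show that the bias could matter, and that the plan as written does not provide the means to find out.

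**What to change.** Reconcile Study population, Outcome measures and the analysis section as follows:

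1. State that outreach use, ICU admissions and cardiac arrest calls are counted per ward over all admissions to that ward, without the HDU/ICU, multiple-transfer or 50%-stay exclusions.
2. Prespecify an analysis of eLOS and of the death/readmission outcomes that re-includes HDU/ICU patients, attributed to the ward they were on before transfer, with the transfer and 50%-stay rules waived for them.
3. Report the number and proportion of patients excluded for HDU/ICU admission by ward and by control or intervention period. The formula above can then be used with observed rates.

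The primary eLOS population may stay as it is, so the planning rates remain applicable.

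The cost is a change of wording, a re-extraction from the same hospital administrative systems, and some added noise in the re-inclusion analysis from long ICU stays. Data collection is described as ongoing and no interim analysis is planned, so the change can be fixed before the data are analysed.
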